#### Intervention

Our study intervention will be the implementation of site-specific HCV treatment workflows. Ad hoc consultation with a hepatologist is already available within the healthcare system, and providers can continue to reach out as needed. This will help ensure high-quality care while reducing unnecessary and expensive specialist visits that further perpetuate barriers to accessing HCV treatment for vulnerable, high-risk patient populations.

### Data collection

Data collection will occur using two main methods: (1) interviews with study participants and (2) data extraction from CUC’s EMR. Data will be extracted from the EMR at enrollment, upon treatment completion, and 12 weeks after treatment completion, when viral load is measured to determine cure, known as sustained virologic response at 12 weeks, or SVR12. Variables collected from the EMR will include the following: HCV RNA PCR test results; primary care physician; laboratory test results used to determine eligibility, including those for HIV (HIV antibody)and HBV (hepatitis B surface antigen); demographic information such as age, sex, gender, race, and ethnicity; medical comorbidities excluding psychiatric diagnoses (the latter will be collected directly from patients); prescriptions for HCV treatment; orders for an HCV genotype test and ultrasound (as “unnecessary” tests to measure fidelity); and dates of medication pickup. Date of first medication pickup will be the proxy for date of treatment initiation.

Data will be captured and stored in REDCap, a HIPAA-compliant, secure data collection tool and database that only the research team members access. Participants’ identifiable data will be retained to enable contact through to the end of the study. Identifiers and identifiable data will be retained for future research on HCV if the study participant provides written informed consent to do so. Since this is a minimal risk study, a data safety monitoring board is not required. The research team will utilize an internal data dashboard to monitor the study progress and data quality. Quality of data collection will also be tracked by the research team. Data quality measures will consist of (1) weekly checks of missing and incomplete data collected from interviews and the EMR by the research assistant and research coordinator and (2) automated monthly reports of the frequency of missing and incomplete data. In some instances, if we find that data from the EMR is frequently missing, the research team may need to discuss collecting the data directly from the patient.

#### Enrollment

Study participants will be enrolled over a 6-month period. Study participants will interact with the research team at one or two time points: upon enrollment and, among those who go on treatment, at the end of treatment completion, which may be approximately 2–3 months from enrollment.

At the time of the patient’s clinic visit, a member of the research team will meet with the patient to describe the study and obtain written informed consent from those willing to participate. Clinic staff will provide an introduction of the eligible patient to the research team, as needed. Research team members will also recruit pre-screened patients from around the clinic setting with the help of clinic staff. The team will work with clinic staff to position themselves within the clinics so as to minimize disruption of workflows and clinical care.

On a biweekly basis, the research team will examine study progress by reviewing enrollment at each study site, including basic demographics of study participants, to ensure enrollment is occurring as intended. The research assistant and research coordinator will monitor study progress weekly. Additionally, we will track reasons why study participants were not treated using the site-specific HCV treatment workflows (e.g., changes in clinical status, lost to follow-up from the clinic). We will also generate estimates of how many study participants are at each step along the HCV care cascade. There will be specific thresholds to trigger an ad hoc review if enrollment is not occurring as intended.

#### First interview at enrollment

The first interview will be conducted by a research team member at time of study enrollment. The face-to-face interview, lasting approximately 20 min including enrollment time, will include questions on medical coverage, education, social support, work, housing, substance use history, mental health disorders and psychiatric diagnoses, and contact information.

#### Second interview at treatment completion

Regimens typically require 8 or 12 weeks of treatment. Upon treatment completion, a laboratory test is performed to measure HCV viral load. This test is repeated 12 weeks after treatment completion (SVR12) to ensure that the response is sustained and the patient is cured of HCV. A viral load < 15 IU/mL is considered undetectable. Record of a laboratory test taken at the time of treatment completion will serve as a proxy for treatment completion. The second, shorter interview will ideally occur when the participants have their blood drawn for this test at treatment completion. Follow-up data will be collected on substance use and sexual behavior during treatment, medication adherence, and treatment side effects. If needed, research team members may reach out to the study participant by phone to arrange a time to meet for the second interview.

In the absence of test results, other markers for treatment completion may be used. These include self-report, date of last bottle pickup + 28 days, or clinical documentation of treatment completion in a note in the EMR. Study participants who do not pick up all treatment doses or do not return for a final laboratory test for viral load will be considered lost to follow-up and will be assumed to have not achieved SVR12.

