### Sample size justification

We predict that we will achieve SVR12 in 75% of patients enrolled in our study. We will use the “intention-to-treat” principle by including those enrolled in the study and lost to follow-up in the denominator. Therefore, the denominator will consist of the population of patients at participating clinical sites who have been screened and diagnosed with chronic HCV infection and who have provided informed consent to participate in our study, regardless of whether treatment was initiated or not. These estimates were based on experience treating HCV in this patient population, as well as three published studies of HCV treatment interventions for people experiencing homelessness in the primary care setting [9, 10, 21].

With the expectation that 75% of patients enrolled in the study will achieve SVR12, a two-sided 95% confidence interval will be constructed with a half-width no more than 5% from the point estimate. In order to assure with 95% confidence that the true proportion achieving SVR12 under the locally contextualized site-specific HCV treatment workflows is within 5% of the observed proportion, the required sample size is 289 patients (Fig. 2).

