### Analytical approach

We will quantify the proportion of the study population with HCV that achieved SVR12, including a confidence interval for this proportion, using the “intention-to-treat” principle as detailed above. Secondary analyses will follow the “per-protocol” approach where the denominator will exclude participants lost to follow-up.

Participants who do not pick up all their HCV medication and who do not complete a final laboratory test for viral load by the end of the trial period will be recorded as not having completed treatment, considered lost to follow-up, and assumed to have not achieved SVR12. Participants who either miss or delay treatment doses or who do not pick up all treatment doses, but return for a treatment completion lab or SVR12, will be retained within the dataset and recorded as non-adherent for descriptive analyses. We will also evaluate the number and proportion of patients moving through each step of the HCV care cascade, from diagnosis of HCV and enrollment to achieving SVR12 in order to better understand barriers within the care cascade. General reasons for failure to initiate and complete treatment will be discussed with clinic staff and summarized, as will delays between each step of the care cascade.

To derive proportions and 95% confidence intervals (95% CI), we will apply generalized estimating equations (GEE) to logistic regression models without predictors and interpret the anti-logit of the intercept as our proportion. Bias-corrected GEE will be applied to account for a small sample size. We will examine characteristics of the patient population stratified by achievement of SVR12. These characteristics will include age, sex, race, ethnicity, housing factors, education, employment status, payor, mental health conditions and psychiatric diagnoses, substance use history, sexual behavior, medical comorbidities, clinical site, and adherence to HCV treatment. These characteristics will also be evaluated after adjusting for covariates using a multivariable logistic regression model. Reported outcomes will include adjusted odds ratios for SVR12 and their 95% confidence intervals. We will use GEE models to account for clustered data and correct for small sample size, as described above. We will also conduct similar exploratory analyses for our secondary outcomes.

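### The rules for treatment completion let a participant with incomplete pickup but an end-of-treatment lab pass as a completer, and a neighbouring rule classes the same participant as lost to follow-up

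*Protocol article*

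**What the plan says.** All references are to the protocol article.

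- **Completion marker** (*Second interview at treatment completion*): "Record of a laboratory test taken at the time of treatment completion will serve as a proxy for treatment completion". Other markers are allowed when no test result is available: "These include self-report, date of last bottle pickup + 28 days, or clinical documentation of treatment completion".
- **Loss to follow-up, either failure suffices** (end of the same section): the rule covers "Study participants who do not pick up all treatment doses or do not return for a final laboratory test for viral load". These participants are treated as lost to follow-up and as not having reached SVR12.
- **Non-completion, both failures needed** (*Analytical approach*): the rule covers "Participants who do not pick up all their HCV medication and who do not complete a final laboratory test for viral load", judged when the trial closes. On status, the plan says that such people "will be recorded as not having completed treatment, considered lost to follow-up, and assumed to have not achieved SVR12".
- **Incomplete pickup with a lab** (*Analytical approach*, next sentence): participants "who do not pick up all treatment doses, but return for a treatment completion lab or SVR12, will be retained within the dataset" and flagged as non-adherent, for description only.
- **Where completion is used**: it is a secondary clinical outcome with all enrolled patients as denominator (*Clinical outcomes*), a RE-AIM effectiveness measure (Table 3), and a step between initiation and SVR12 in the care cascade (*Analytical approach*).
- **Data at hand** (*Data collection*): the EMR extract includes HCV prescriptions and "dates of medication pickup". The first pickup date stands in for treatment start.

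**The concern.** A viral-load test at the expected end of treatment shows that the participant attended. It does not show that the whole course was obtained. Because the lab record ranks first and pickup is consulted only when the lab is absent, incomplete pickup has no influence on completion status once a lab exists. The plan expects such participants, since it has a sentence for them.

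Two things are at stake. First, initiation is measured by pickup and completion by lab attendance. A participant who collects part of the course and then has the test does not appear as a loss between those two cascade steps, so for this group any error in the completion proportion is upward.

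Second, the rules conflict beyond completion. Under the either-failure sentence, a participant with incomplete pickup and an undetectable SVR12 result is a primary-outcome failure and, as lost to follow-up, leaves the per-protocol denominator. Under the Analytical approach, the same participant is retained and can count as cured.

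**Working it through.** **1. The plan's own figure.** The only related number is the sample size. *Sample size justification* gives the planning value: "With the expectation that 75% of patients enrolled in the study will achieve SVR12", with a two-sided 95% interval of half-width 0.05.

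n = z² p(1 − p) / h² = 1.96² × 0.75 × 0.25 / 0.05² = 288.11, rounded up to **289**.

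The stated 289 is reproduced, and the half-width at 289 is 4.99 points. The figure serves below only as denominator and yardstick, because the point is a coding rule.

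**2. The rules applied to each type of participant who started treatment.**

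| Participant | Completion marker (*Second interview*) | Either-failure sentence (*Second interview*) | *Analytical approach* |
|---|---|---|---|
| A. Full pickup, completion lab and SVR12 test | Met | Not lost | Not a non-completer |
| B. Incomplete pickup, completion lab and SVR12 test | **Met by the lab** | **Lost to follow-up, SVR12 failure** | **Retained, non-adherent; not recorded as a non-completer** |
| C. Incomplete pickup, SVR12 test only | Not met by a completion lab; fallback markers possible | Lost to follow-up, SVR12 failure | Retained, non-adherent; completion not stated |
| D. Incomplete pickup, no lab | Not met by a lab; fallback markers possible | Lost to follow-up, SVR12 failure | Not completed, lost to follow-up, SVR12 failure |

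For A the rules agree. For D the Analytical approach states non-completion outright. The problem sits in B and, less clearly, in C. B meets the completion marker and escapes the one sentence that assigns non-completion, yet is lost to follow-up under a sentence in the same section as the marker.

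**3. Size, by assumption.** The documents do not give the share of participants in group B. Taking that share s of the 289 enrolled, the number reclassified if full pickup is required is k = 289s, rounded, and the fall in the completion proportion is k / 289:

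| Assumed s | k | Fall in completion |
|---|---|---|
| 1% | 3 | 3/289 = 1.0 points |
| 5% | 14 | 14/289 = 4.8 points |
| 10% | 29 | 29/289 = 10.0 points |

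**4. The same question from the lab side.** Assume that 80% of the 289 (231, or 79.9%) have the end-of-treatment lab and that a share g of those had incomplete pickup:

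| Assumed g | Completers if full pickup is required | Proportion |
|---|---|---|
| 2% | 226 | 226/289 = 78.2% |
| 5% | 219 | 219/289 = 75.8% |
| 10% | 208 | 208/289 = 72.0% |
| 20% | 185 | 185/289 = 64.0% |

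At g = 5% the gap is 4.2 points, close to the 5-point precision planned for SVR12. At g = 10% it is 8.0 points and exceeds it.

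**The case against.** **The plan nowhere says that these participants are completers.** A reader might infer that it settles this. It does not. The Analytical approach calls them retained and non-adherent, and the either-failure sentence makes them lost to follow-up, a status that the Analytical approach ties to non-completion. This objection stands and limits the point: the coding is contradictory, and one of its readings overstates completion. It does not remove the need to act, since that sentence assigns follow-up and SVR12 status and does not mention completion.

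**The proxy requires a test at the end of treatment, not any blood draw.** This is fair, and it is why group C is not clearly affected. But the plan itself foresees participants who have incomplete pickup and still return for that test.

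**These participants stay identifiable.** This is also true. The non-adherence flag, the adherence questions at the second interview and the summary of reasons for not completing all help, so the drop-off is not wholly hidden. The flag also covers missed or delayed doses, however, and does not change the completion count.

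**Pickup is a proxy too.** It does not prove ingestion. The workflows may include drug delivery through street or community care, and the plan anticipates that some EMR items will often be missing. This stands as a cost of the fix. Even so, pickup speaks to whether the full course was obtained, which a viral-load result does not.

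Two further inferences are tempting but unsupported:

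- **The last-pickup fallback has the same defect.** The wording may well mean the last bottle of the course, so it is ambiguous at most.
- **A misdated completion makes false cure more likely.** If a participant stopped before the lab, counting from the lab places the SVR12 test later after the last dose, and the primary outcome accepts tests at 12 weeks or later.

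**Conclusion.** The point holds in a limited form. Under the lab proxy and the both-failures rule, a participant with incomplete pickup and an end-of-treatment lab meets the completion marker and is not recorded as a non-completer. That can overstate the secondary outcome and the initiation-to-completion step. The either-failure sentence points the other way, so the protocol does not fix one coding for this group, and the same conflict reaches SVR12 and the per-protocol denominator.

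The direction for this group is upward, but the size is unknown. The 1, 5 and 10 point figures rest on assumed shares of 1%, 5% and 10% and should not be read as an established overstatement. The effect may be small. The correction is worth making because completion is a named outcome and the rule is cheap to repair.

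**What to change.** - **Define completion for analysis from pickup.** A participant has completed treatment when every bottle of the prescribed course was picked up, judged from the prescriptions and pickup dates already extracted.
- **Incomplete pickup means not completed**, even when an end-of-treatment lab exists.
- **Keep the other markers as a fallback.** Use the lab record, self-report or chart note only where pickup data are missing, and report the number classified that way separately.
- **Reconcile the two rules.** The either-failure sentence in *Second interview at treatment completion* and the both-failures sentence in *Analytical approach* must give each participant one status.
- **Separate the concepts.** Completion, loss to follow-up and SVR12 status should each have their own definition, so that none is inferred from another.

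The cost is a change of wording and coding, with no new visits or data items. Pickup does not prove ingestion, pickup records may be missing for some delivered medication, and the reported completion proportion may be slightly lower.

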### Evaluation of study clinical and implementation outcomes

#### Clinical outcomes

The primary outcome will measure the proportion of patients with chronic HCV infection enrolled in the study that achieves SVR12 (cure) as defined by an undetectable viral load < 15 IU/mL at 12 weeks or later after treatment completion.

The secondary clinical outcomes measure is as follows:Time (in days) from being offered treatment to initiating treatment, among those enrolled in the studyProportion of patients enrolled in the study who initiate HCV treatmentProportion of patients enrolled in the study who complete HCV treatment

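### Two conflicting lost-to-follow-up rules make a patient with incomplete pickup and an undetectable SVR12 result a failure in one section and a cure in another, and leave the per-protocol denominator unsettled

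*Protocol article*

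**What the plan says.** Four places in the protocol article bear on this.

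- **Second interview at treatment completion** (last sentence): it states that those who "do not pick up all treatment doses or do not return for a final laboratory test for viral load will be considered lost", and the same sentence presumes that these patients did not reach SVR12. Incomplete pickup alone is enough, and so is a missing final test.
- **Analytical approach**: "Participants who do not pick up all their HCV medication and who do not complete a final laboratory test for viral load" before the trial closes get the same label and the same presumed failure. Here both conditions must hold.
- **Analytical approach**, next sentence: this covers those "who do not pick up all treatment doses, but return for a treatment completion lab or SVR12, will be retained within the dataset"; such patients are "recorded as non-adherent for descriptive analyses".
- **Clinical outcomes**: cure is a viral load below 15 IU/mL "at 12 weeks or later after treatment completion". Pickup is not a condition.

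Two denominators follow. Sample size justification puts every consenting enrolee in the primary denominator, treated or not. Analytical approach adds a per-protocol "approach where the denominator will exclude participants lost to follow-up".

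**The concern.** The two rules attach the same label and the same consequence to different sets of patients. The sentence on retained patients shows that the AND in Analytical approach is not a loosely written OR: it gives incomplete pickup with a returned lab the opposite handling from the interview section.

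For the primary outcome, the OR rule overrides an observed undetectable viral load at the qualifying time and so lowers the estimate. For the per-protocol analysis, the same rule removes partially treated patients whose virus was observed to be detectable, while the AND rule keeps them. If the choice is left open until the data are in, the primary numerator and the per-protocol denominator can be settled by whichever sentence is followed.

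**Working it through.** **1. The plan's own figure.** Inputs from Sample size justification: p = 0.75, half-width d = 0.05, two-sided 95% confidence.

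n = 1.96² × p(1 − p) / d² = 3.8415 × 0.1875 / 0.0025 = 288.11, rounded up to 289.

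The half-width at 289 is 1.96 × √(0.1875/289) = 4.99 points. The stated 289 is reproduced and this point does not affect it.

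**2. The rules side by side.**

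| Pattern | OR rule (Second interview) | AND rule and next sentence (Analytical approach) | Primary status under Clinical outcomes |
|---|---|---|---|
| A. Full pickup, SVR12 test done | not lost | not lost | viral load decides |
| B. Incomplete pickup, undetectable at 12 weeks or later | lost, presumed failure | retained | cure |
| C. Incomplete pickup, detectable at 12 weeks or later | lost, presumed failure | retained | non-cure |
| D. Incomplete pickup, treatment-completion lab only | lost, presumed failure | retained | non-cure |
| E. Full pickup, no final lab | lost, presumed failure | AND condition not met | non-cure |
| F. Incomplete pickup, no lab | lost, presumed failure | lost, presumed failure | non-cure |

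Only B changes status on the primary outcome. C, D and E are non-cures there under either rule, but they move in or out of the per-protocol denominator.

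**3. Size on the primary outcome.** The frequency of B is not given, so shares of 2%, 5% and 10% of 289 are assumed (6, 14 and 29 patients). Start from 217/289 = 75.1% with B counted as cures, then apply the OR rule:

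- 6 patients: 211/289 = 73.0%, a fall of 2.1 points
- 14 patients: 203/289 = 70.2%, a fall of 4.8 points
- 29 patients: 188/289 = 65.1%, a fall of 10.0 points

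About 14 such patients use up nearly the whole planned 5-point half-width.

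**4. Size on the per-protocol proportion.** The two sources are taken separately, again with assumed counts.

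*Pattern E.* Take 217 cures and suppose nobody else is excluded. Keeping E gives 217/289 = 75.1%. Dropping 6, 14 or 29 such patients gives 217/283 = 76.7%, 217/275 = 78.9% or 217/260 = 83.5%.

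*Patterns B and C.* Suppose 185 patients have full pickup and an SVR12 test (180 undetectable), and 12 have incomplete pickup and an SVR12 test (9 undetectable, 3 detectable). The OR rule gives 180/185 = 97.3%. Retaining the 12 gives 189/197 = 95.9%, a difference of 1.4 points.

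**The case against.** The best defence is that the article already points to the answer. Clinical outcomes defines cure by viral load alone. Analytical approach, the section an analyst would follow, deals explicitly with incomplete pickup and a returned lab. The OR sentence sits in a data-collection section and is the outlier. This stands as an argument about which rule was probably intended. It does not remove a current sentence that declares an observed cure a failure.

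It is also fair that the frequency of pattern B is unknown, and that leaving partially treated patients out of a per-protocol analysis is ordinary practice. The fault is that the text supports both leaving them out and keeping them in. The planned report of non-adherent patients among those cured, at the end of Analytical approach, is weak support for counting pattern B as cures. It describes non-adherence as missed or delayed doses, which can occur with full pickup.

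Four stronger readings are tempting, and the documents do not support them:

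- *Patients with full pickup and no SVR12 test have no primary outcome.* They do. Clinical outcomes requires an undetectable result and Sample size justification keeps them in the denominator, so they are non-cures.
- *A treatment-completion lab alone could count as cure.* Clinical outcomes fixes the timing at 12 weeks or later. Being retained in the dataset is not being cured.
- *The per-protocol result could swing by some 14 points.* On the counts in step 4, that needs a further 30 untested full-pickup patients kept as failures under one rule only: 189/(197 + 30) = 83.3% against 97.3%. The AND sentence does not exclude them, but nothing says they are to be scored that way. Without them the gap is 1.4 points.
- *The per-protocol proportion is the only secondary analysis of SVR12.* Multivariable models for SVR12 and an analysis of fidelity against the primary outcome are also planned.

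**Conclusion.** The contradiction is real, lies in the current text, and reaches the primary outcome through one group: incomplete pickup with an undetectable viral load at 12 weeks or later. That group is a failure under the interview section and a cure under Clinical outcomes and Analytical approach. If it makes up 2% to 10% of enrolees, the primary estimate differs by about 2 to 10 points. Those shares are assumptions, because the documents give no count. The per-protocol denominator is also undetermined, for full pickup without a final lab and for incomplete pickup with a returned lab, including patients with detectable virus. No pattern of pickup and testing is a cure, a failure and unclassified all at once, and the sample size is unaffected. The rules should be reconciled before outcomes are classified.

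**What to change.** Amend the last sentence of Second interview at treatment completion and the matching sentence of Analytical approach so that both state one rule consistent with Clinical outcomes:

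- SVR12 is classified by the viral load at 12 weeks or later after treatment completion, regardless of pickup.
- Every enrolee without a qualifying undetectable result is a non-cure in the primary analysis.
- Lost to follow-up means no qualifying SVR12 viral load by the end of the trial. This single definition sets the per-protocol denominator.
- Completeness of pickup is used only to describe adherence.

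The cost is wording in two sections and a change to the outcome derivation code. No new data are needed and the sample size of 289 stays.
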